Although molecular imaging allows reliable information on in vivo dopaminergic function [68], no studies, to our knowledge, has examined dopaminergic system activity in PTSD patients using molecular neuroimaging techniques.

The main reasons that justify such an effort to understand the problem of violence and its consequences for mental health can be described as follows: 1) Treatment strategies to be sponsored by the Brazilian public health care system need to be based on solid local data on the extent and nature of the disorder; 2) Exposure to traumatic life events is related to not only with mental disorders which include PTSD and depression, but also with other cognitive and neurotransmission dysfunctions [18,19,44,69]. The impact in mental health of the population of exposure to violence among the population of Sao Paulo, a large urban centre in a Middle Income Country (MIC), as well as specific parameters such as neurocognitive, neurostructural anf functional neuroimaging finds is virtually unknown.

The subjects of the study will be selected from an epidemiological/genetic survey in the city of Sao Paulo to assess the relationship between exposure to violence and the prevalence of PTSD and common mental disorders. Subjects located in the epidemiological/genetic survey will be referred to these three case-control studies, reported here, and to a randomized controlled clinical trial on the efficacy of topiramate for the treatment of PTSD symptoms.

This protocol is the result of collaborative task force to conduct translational research in the field of traumatic stress in urban regions of Brazil. The current project investigates possible causes for neurocognitive deficits, neurostructural changes and dopaminergic dysfunction in individuals with PTSD. We will be comparing individuals with current or lifetime diagnosis of PTSD with those who were exposed to a traumatic event but did not develop a current or a lifetime diagnosis of PTSD.

The main objectives of this project are:

1. to examine cognitive functioning of PTSD subjects and its relationships with symptomatology;

2. to evaluate neurostructural integrity of orbitofrontal cortex and hippocampus in PTSD subjects;

3. to evaluate if patients with PTSD have decreased dopamine transporter density in the basal ganglia as compared to resilient controls subjects.

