## Methods and design

### Sample

Cases and controls will be identified through an epidemiologic survey conducted in the city of São Paulo. Details of the epidemiologic study are presented in a companion paper (cite) and are summarized here. To identify trauma victims in the community, interviews were conducted by a professional team specialized in household surveys, the Brazilian Institute of Public Opinion and Statistics. Interviewers were trained at the CIDI [70] in the Federal University of São Paulo, an accredited center by the World Health Organization (WHO). Training procedures were conducted in accordance to the guidelines set up by the WHO. Interviews were carried out in the participants households by means of printed questionnaires. All questionnaires were translated into Portuguese and adapted to the local social and cultural context. Inclusion and exclusion criteria for the three case-control studies are described in tables 1 and 2, respectively. Individuals who met inclusion criteria during the epidemiologic study were invited to participate in the case-control study. Subjects exposed to traumatic life experiences resulting in PTSD (cases) will be compared to resilient subjects victims of traumatic life experiences without PTSD (controls) aiming to identify biological variables that might protect or predispose to PTSD. This case-control design will enrol representative subjects from the community being this procedure an important technique to overcome Berkson bias. Subjects will be informed about the procedures of the studies and will be asked to formally consent willingness to participate. Subjects who consent to participate in the case-control studies will receive the following assessment:

**Table 1 T1:** Inclusion criteria for PTSD cases (p) and control (c) groups

	Neuropsychological Study		Structural Neuroimaging study		Molecular Neuroimaging study	
	p	C	P	c	p	c
Age between 18 and 60 (inclusive)	X	X	X	X	X	X
Life time history of traumatic life experience as defined in criteria A of DSM IV criteria for PTSD	X	X	X	X	X	X
PTSD diagnosis according DSM IV criteria as assessed by SCID I applied by trained psychiatrists or psychologists	X		X		X	
Good general health with no additional diseases expected to interfere with the study	X	X	X	X	X	X
Able to understand and signed informed consent	X	X	X	X	X	X
Completed 5 years grades of education	X	X				
						
Fluent in Portuguese	X	X	X	X	X	X
Willing and able to complete all assessments	X	X	X	X	X	X

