#### Data management and Analyses

1) Questionnaires will be double typed and data will be entered on SPSS software data files. Participants will be divided into two categories, according to the diagnosis: (1) lifetime diagnosis of PTSD and (2) Traumatic experience, but no lifetime diagnosis of PTSD. The following comparisons will be carried out in the two groups:

1) Neuropsychological Study: neuropsychological measures of PTSD cases compared to controls;

2) Magnetic resonance imaging study: to assess neurostructural abnormalities in OFC and hippocampus of patients with PTSD compared to resilient controls;

3) Molecular neuroimaging study: dopamine transporter density using single photon emission tomography of PTSD cases compared to controls.

Data will be codified and analyzed using the Statistical Package for Social Sciences (SPSS for Windows, version 15.0). Proportion differences will be compared using the Chi Square test or Fisher's exact test, as appropriate. Continuous variables will be compared by Analysis of Variance (ANOVA) or Mann-Whitney test for non-parametric data. All significant tests will be considered as 2-tailed. P values < 0.05 will be considered statistically significant. Because of the exploratory nature of the study, we do not consider alpha adjustment in multiple comparisons and we did not calculate the sample size (Table 3). The main analyses will examine the relationship between exposure to traumatic events and the PTSD occurrence. Unadjusted relative risk for studied variables cognition, cortisol level, hippocampal volume, and dopamine transporter density (and 95% confidence intervals) are presented for trauma without PTSD and trauma with PTSD, both with and without adjustment for age (18–29 years, 30–39 years, 40–49 years, 50–60) and gender. As a secondary analysis, we will be adjusting for clinical and demographic variables previously associated with PTSD: marital status, country of birth, socio-economic status, urbanicity and employment status.

**Table 3 T3:** Sample size in each study for PTSD cases and control groups

	Neuropsychological study		Structural Neuroimaging study		Molecular Neuroimaging study	
	
	Case	Control	Case	Control	Case	Control
Number of individuals for each group	100	100	60	60	25	25

PTSD = Posttraumatic stress disorder; MRI = Magnetic Resonance Imaging

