Despite the unquestionable progress in identification of neurocognitve and neuroanatomical abnormalities associated with PTSD over the past decade or so, it remains unclear whether neurostructural and neuropsychological alterations are specific to PTSD or are related to unspecific environmental factors such as stress and substance abuse. The findings from this neuropsychological study, together with data from neurostructural investigation, may offer an uncommon opportunity to examine the convergence of cognitive and neuroanatomical alterations in patients with PTSD. Stress-induced functional and structural alterations in hippocampus and OFC may mediate many of the symptoms of PTSD that are related to memory dysregulation and hyperexcitability. Interestingly, reversion of both neuropsychological and neuroanatomical abnormalities has been demonstrated after treatment with paroxetine, which in turn has been shown to promote neurogenesis in animal studies [97]. The increasing use of sophisticated neuroimaging techniques is certainly enhancing our understanding of PTSD, potentially improving prevention, treatment, and cognitive rehabilitation programs [23].

Although a previous study showed involvement of DAT gene in PTSD [67], and other indirect investigations have suggested a connection between dopaminergic system and stress [61], insufficient research has been done on the role of the DAT in relation to PTSD. To the best of our knowledge this will be the first SPECT study investigating dopamine transporter density in patients with PTSD and well matched resilient controls coming from an epidemiologic sample. The results of this study will help to disentangle whether possible dopaminergic changes in PTSD are a "state condition" or a "trait" marker of this disorder, raising a discussion why some subjects exposed to trauma develop PTSD and some others do not. Moreover, further studies evaluating patients with PTSD, resilient controls and healthy control subjects (who never experienced trauma) would provide useful information to clarify whether dopaminergic abnormalities are related to PTSD itself or to psychological trauma exposure.

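### The analysis labelled as main, trauma exposure against PTSD, cannot be estimated because every participant is exposed; the list of adjusted estimates names cortisol, which has no described source, and omits orbitofrontal volume

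*Protocol article*

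**What the plan says.** All references are to the protocol article.

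- **Label.** Data management and Analyses says: "The main analyses will examine the relationship between exposure to traumatic events and the PTSD occurrence".
- **Eligibility.** In Table 1, the criterion "Life time history of traumatic life experience as defined in criteria A of DSM IV criteria for PTSD" is marked for both cases and controls in each of the three studies.
- **Groups.** Data management and Analyses divides participants into "1) lifetime diagnosis of PTSD and (2) Traumatic experience, but no lifetime diagnosis of PTSD". The end of the Background describes the comparison group as "those who were exposed to a traumatic event but did not develop a current or a lifetime diagnosis of PTSD".
- **No unexposed group.** The Discussion leaves that to later work: "further studies evaluating patients with PTSD, resilient controls and healthy control subjects (who never experienced trauma) would provide useful information".
- **Listed comparisons.** Before the sentence on the main analyses, the same section lists one comparison per study: neuropsychological measures, OFC and hippocampus, and dopamine transporter density. Each compares PTSD cases with controls.
- **Estimates.** Directly after that sentence, the section announces "Unadjusted relative risk for studied variables cognition, cortisol level, hippocampal volume, and dopamine transporter density (and 95% confidence intervals") for the two trauma-exposed groups, with and without adjustment for age band and gender.
- **Objective 2.** At the end of the Background it reads: "to evaluate neurostructural integrity of orbitofrontal cortex and hippocampus in PTSD subjects".

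**The concern.** The sentence that names the main analysis asks whether trauma exposure is related to PTSD. A design that admits only trauma-exposed people cannot answer that. It is closer to the aim the Background gives the parent survey, on exposure to violence and PTSD prevalence, than to any of the three objectives here.

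The list of variables that get interval estimates and adjustment does not match what the article measures either. It has one entry with no described data source, and it lacks one of the two structures named in objective 2.

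What is at stake is clarity about which results are primary. The section states that there is no sample-size calculation and no adjustment for multiple comparisons. The naming of the main analysis is then one of the few safeguards against choosing results afterwards, and here it points to a quantity that cannot be computed.

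**Working it through.** The plan states no figure for this point and says that no sample size was calculated, so there is nothing to reproduce. The check has three parts.

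**1. Can exposure against PTSD be estimated?**

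Inputs: group sizes from Table 3 (the Abstract gives 50 and 50 for the structural study) and the trauma criterion in Table 1. Let *a* and *b* be exposed cases and controls, and *c* and *d* unexposed cases and controls. Table 1 forces *c* = *d* = 0.

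| Study | a | b | c | d | Exposed share p = (a+b)/n | p(1−p) | PTSD share, exposed a/(a+b) | PTSD share, unexposed c/(c+d) |
|---|---|---|---|---|---|---|---|---|
| Neuropsychological | 100 | 100 | 0 | 0 | 200/200 = 1 | 0 | 100/200 = 0.50 | 0/0 |
| Structural, Table 3 | 60 | 60 | 0 | 0 | 120/120 = 1 | 0 | 60/120 = 0.50 | 0/0 |
| Structural, Abstract | 50 | 50 | 0 | 0 | 100/100 = 1 | 0 | 50/100 = 0.50 | 0/0 |
| Molecular | 25 | 25 | 0 | 0 | 50/50 = 1 | 0 | 25/50 = 0.50 | 0/0 |

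- Odds ratio = (a × d)/(b × c); for the neuropsychological study (100 × 0)/(100 × 0) = 0/0.
- Relative risk = 0.50/(0/0), undefined.
- Chi-square: the expected counts in the unexposed row are 0, so the statistic is undefined.

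The result is the same in every study and for either structural sample size.

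**2. Does the list of estimates match what is measured?**

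Inputs: the four listed variables ("cognition, cortisol level, hippocampal volume, and dopamine transporter density"), the Measures sections and the objectives.

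| Variable | In an objective | Measurement described | In the list of estimates |
|---|---|---|---|
| Cognition | 1 | Yes, neuropsychological battery | Yes |
| Hippocampal volume | 2 | Yes, manual tracing | Yes |
| OFC volume | 2 | Yes, manual tracing in its own section | **No** |
| Dopamine transporter density | 3 | Yes, SPECT binding potential | Yes |
| Cortisol | None | **No** sample or assay described | Yes |

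Three of the four listed variables have a described measurement. Of the four measured target domains, OFC is the one left out. Cortisol is named nowhere else in the article; glucocorticoids and the stress-hormone axis appear only as background.

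**3. Is relative risk the right measure for the listed variables?**

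The 0.50 in the first table comes from recruiting equal numbers of cases and controls. It does not estimate how often trauma leads to PTSD. A relative risk of PTSD by level of a marker would depend on that chosen ratio, so it cannot be estimated directly from these samples. An odds ratio or a mean difference between the groups can be.

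**The case against.** The strongest reply is that one sentence is being read apart from its surroundings. The same section defines the two groups correctly, lists a correct comparison for each study, gives tests (ANOVA or Mann-Whitney, two-sided, 0.05), and in the next sentence contrasts trauma-exposed people with and without PTSD. That stands. A reader might infer that the section fails to describe the analysis of these studies, or that the plan answers none of its objectives. The documents do not support that: the listed comparisons cover objectives 2 and 3 and the case-control part of objective 1. What the reply does not remove is the conflict between those comparisons and the sentence carrying the label of main analysis.

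Second, exposure need not mean yes or no. The Background cites a dose-response relation with severity of exposure, and the Measures include the CAPS, the Early Trauma Inventory (ETI) and the PDEQ. A graded exposure would vary among exposed participants. This limits the claim to exposure yes/no, which is how the sentence reads. The section defines no graded exposure for this analysis, and the ETI, an obvious candidate, covers early-life trauma only.

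Third, a reader might infer that cortisol is not collected at all, or that OFC is dropped from the analysis. Neither is supported. Participants come from a survey reported in a companion paper that is not shown, so the article supports only that it describes no cortisol collection. OFC is in the list of group comparisons; what it lacks is the interval estimate with age and gender adjustment.

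Finally, the study is declared exploratory, and no sample size or error rate hangs on the label. That lowers the severity, but it does not make the stated analysis estimable.

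**Conclusion.** The point holds in a limited form. As worded, the main analysis cannot be estimated: exposure yes/no is 1.00 in both groups of all three studies. It also conflicts with the case-control comparisons earlier in the section, which do match the objectives. In the list of estimates, one of four entries has no described source, and one of the two structural targets of objective 2 is missing, so OFC is left with only the unadjusted group test.

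This rests on reading exposure as yes/no, since no graded measure is named, and on the article alone, since a source for cortisol may exist elsewhere.

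Severity: should fix. A must-fix grade would be tempting because the error sits in the sentence naming the main analysis. It is not warranted, because valid comparisons already stand in the section and the correction changes no recruitment or assessment.

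**What to change.** Replace the sentence on the main analyses and the one after it with wording to this effect:

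- Among trauma-exposed participants, the main analyses compare PTSD cases with resilient controls on (a) the neuropsychological scores, (b) hippocampal and orbitofrontal volumes, and (c) striatal dopamine transporter binding potential, each with and without adjustment for age and gender.
- Report the results as mean differences or odds ratios with 95% confidence intervals, in place of relative risks. Adding OFC to the present list without this change would only extend the relative-risk problem to another variable.
- Delete cortisol, or state where the measurement comes from and which participants have it.
- If a graded trauma exposure is intended, name the measure and make it a separate analysis. If the ETI is chosen, say that it covers early-life trauma only and does not grade adult or index trauma.

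The cost is analysis wording, plus one more adjusted model for OFC from data already planned. If cortisol is kept, its source must also be documented.

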#### Ethical Issues

Participants will be informed about research procedures and risks and signed an informed consent submitted and approved by the Ethical Committee of the Federal University of São Paulo (Processes: 1-Neuropsychology-0124/06; Neurostructural-1026/06; Molecular neuroimaging-0295/06). Subjects diagnosed as having any mental health disorder will be offered a referral to the out-patient clinic at the Federal University of Sao Paulo.

## Discussion

This study protocol illustrates a collaborative work of potential value to researchers interested in innovative and realistic investigation aimed at understanding the neurobiology of PTSD in a population-representative sample. This article describes the methodological responses to challenges in conducting translational research, where patients are identified from a real-world scenario in a population-based study and go through neuropsychological, neurostructural and molecular neuroimaging techniques.

A recent review of the literature found over 60 studies examining memory and attention performance in PTSD subjects, but few studies have examined learning, executive functioning, and emotional reaction in this population. A key aim of the present neuropsychological study is not only to assess those less explored domains but, also, try to clarify some discrepancies reported in literature by examining a more homogeneous, adequately controlled sample. Some inconsistencies in neuropsychological findings may be attributed at least in part to sample limitations. Neuropsychological deficits involving attention and memory have been replicated in different samples including war veterans [14,15,20], rape victims, and other traumatized populations. However, most neuropsychological studies of PTSD involve war veterans with chronic PTSD who frequently exhibit comorbid psychiatric conditions such as depression, anxiety and substance use disorders, which represent major confounders [15]. The effects of depressed mood on neuropsychological functioning have been well documented [96]. The high rate of comorbidity and overlap of symptoms between these two disorders, however, makes it difficult to exclude individuals with current depression from PTSD studies. Therefore, it is important to address the presence of comorbid depression and to include measures of depression as covariates in analyses.

Despite the unquestionable progress in identification of neurocognitve and neuroanatomical abnormalities associated with PTSD over the past decade or so, it remains unclear whether neurostructural and neuropsychological alterations are specific to PTSD or are related to unspecific environmental factors such as stress and substance abuse. The findings from this neuropsychological study, together with data from neurostructural investigation, may offer an uncommon opportunity to examine the convergence of cognitive and neuroanatomical alterations in patients with PTSD. Stress-induced functional and structural alterations in hippocampus and OFC may mediate many of the symptoms of PTSD that are related to memory dysregulation and hyperexcitability. Interestingly, reversion of both neuropsychological and neuroanatomical abnormalities has been demonstrated after treatment with paroxetine, which in turn has been shown to promote neurogenesis in animal studies [97]. The increasing use of sophisticated neuroimaging techniques is certainly enhancing our understanding of PTSD, potentially improving prevention, treatment, and cognitive rehabilitation programs [23].

Although a previous study showed involvement of DAT gene in PTSD [67], and other indirect investigations have suggested a connection between dopaminergic system and stress [61], insufficient research has been done on the role of the DAT in relation to PTSD. To the best of our knowledge this will be the first SPECT study investigating dopamine transporter density in patients with PTSD and well matched resilient controls coming from an epidemiologic sample. The results of this study will help to disentangle whether possible dopaminergic changes in PTSD are a "state condition" or a "trait" marker of this disorder, raising a discussion why some subjects exposed to trauma develop PTSD and some others do not. Moreover, further studies evaluating patients with PTSD, resilient controls and healthy control subjects (who never experienced trauma) would provide useful information to clarify whether dopaminergic abnormalities are related to PTSD itself or to psychological trauma exposure.

Advances in molecular imaging techniques, such as SPECT, have made important contributions to the understanding of the pathophysiology of neuropsychiatric disorders [98]. Molecular imaging approaches are more sensitive than Neuroanatomical imaging techniques, and are able to identify subtle cerebral pathophysiological changes before neurostructural abnormalities take place. One of the major goals of molecular imaging research has been the identification of biomarkers, which are defined as the characteristics that are objectively measured and can differentiate normal biologic processes from pathogenic processes. These approaches has the potential to provide accurate and early neuropsychiatric recognition, evaluate disease progression, and monitor treatment efficacy [68].

These studies have several important limitations. First, cases are recruited after they have developed PTSD. Assuming we find differences between cases and controls on neuropsychological/imaging variables, we will not be able to determine whether these differences reflect a risk factor or a consequence of the disorder. Second, in several situations both cases and controls, were exposed to traumatic experience years before the investigations, producing a potential recall bias.

This study protocol intends to be helpful for researchers and clinicians interested in designing and/or conducting translational research in the field of trauma and posttraumatic stress disorder.
